#### Secondary outcome measures

• Death before hospital discharge

• Duration of hospital stay

• Duration of intensive and high dependency care (Appendix 2)

• Duration of parenteral nutrition

• Change in Z score for weight and head circumference from birth to 36 weeks post-

conceptional age and from birth to discharge

• In continuous supplemental oxygen at 36 weeks post-menstrual age

• Confirmed bacterial sepsis (Appendix 3)

• Gastrointestinal perforation

• Gastrointestinal surgery

• Cholestasis (defined as >25 μmol/l conjugated fraction of serum bilirubin)

• Patent ductus arteriosus requiring pharmacological or surgical treatment

• Cranial ultrasound abnormality

• Type of milk at discharge

• On oxygen therapy at discharge

No additional blood tests will be performed because of this study.

### Data collection

Data will be collected at trial entry, during the infant's stay in the neonatal unit, and at discharge. At trial entry baseline data and eligibility information will be collected and returned to the co-ordinating centre. Information collected during the infant's stay in the neonatal unit will include enteral feeding history (to assess compliance) and other treatments given (to assess whether interventions are used differentially in the two groups). This is important because caregivers will not be blinded to the randomised allocations. Outcome data will be recorded on a form competed by clinicians at discharge. To facilitate later tracing for follow-up and enable notification of any deaths, all infants recruited to the study will be flagged at the NHS Central Register.

All data required for trial analysis will be routinely collected in medical and nursing charts.

Perinatal and early neonatal data will be submitted to the ADEPT Co-ordinating Centre at time of trial entry. Subsequent neonatal data and outcome data will be submitted at discharge *and on transfer to a different neonatal unit if applicable*. Growth data - weight and head circumference - will be collected at 36 weeks post-menstrual age *and *at discharge.

### Serious Adverse Event and Suspected Unexpected Serious Adverse Reaction reporting

Serious Adverse Events and Suspected Unexpected Serious Adverse Reactions should be reported to the ADEPT co-ordinating office within 48 hours. The co-ordinating office will then report it to the Chair of the DMEC and the MREC with a summary of the previously reported events within 15 days. As both early and late feeding policies are already used in different hospitals within the UK there are no SAEs which would be anticipated as a unique consequence of participation in the trial. We would however expect the following to be reported:

• All deaths

• Severe central venous line complication: cardiac tamponade, major vessel thrombosis

Any other serious unexpected adverse events

### Statistical analysis

Analysis will be by intention to treat i.e. all babies will be analysed in their allocated groups, regardless of the treatment they actually received. For dichotomous outcomes, relative risks and 95% confidence intervals will be calculated. For continuous outcomes, differences in means or differences in medians (depending on the distribution of the data) will be calculated along with 95% confidence intervals. Analysis of time to event outcomes such as time to reach full enteral feeding and duration of stay in hospital will use survival analysis techniques.

Two pre-specified subgroup analyses will be conducted, stratifying by (a) gestational age at birth (< or ≥ 29 weeks) and (b) type of Doppler abnormality (AREDFV or cerebral redistribution). Statistical tests of interaction will be used for the subgroup analyses. Interim analyses will be conducted at least once per year during the period of recruitment, and reviewed in confidence by a Data Monitoring Committee.

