**Methods and Design:**

Babies with gestational age below 35 weeks, and with birth weight below 10th centile for gestational age, will be randomly allocated to an "early" or "late" enteral feeding regimen, commencing milk feeds on day 2 and day 6 after birth, respectively. Feeds will be gradually increased over 9-13 days (depending on gestational age) using a schedule derived from those used in hospitals in the Eastern and South Western Regions of England, based on surveys of feeding practice. Primary outcome measures are time to establish full enteral feeding and necrotising enterocolitis; secondary outcomes include sepsis and growth. The target sample size is 400 babies. This sample size is large enough to detect a clinically meaningful difference of 3 days in time to establish full enteral feeds between the two feeding policies, with 90% power and a 5% 2-sided significance level. Initial recruitment period was 24 months, subsequently extended to 38 months.

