#### Recruitment and randomisation

Informed written consent for the trial will be obtained from the parents in the first 2 days after birth. This will preferably be in the first 24 hours after birth. The parents will be given a verbal explanation of the study and a written information sheet, and will have an opportunity to discuss participation with the recruiting clinician. If consent is given, and providing no contra-indications occur, the baby should then be randomised between 20 and 48 hours of age. Babies will be randomised to study groups by a central randomisation service, based at the National Perinatal Epidemiology Unit (NPEU), University of Oxford. The randomisation service (website with telephone back-up facility) will request details of the baby and, if eligible, will provide a random allocation to one of the study groups, either "early" or "late" commencement of enteral feeds. The program will use minimisation to ensure balance between the groups with respect to hospital of recruitment, gestational age (< 29 completed weeks or ≥ 29 completed weeks) and type of Doppler abnormality (AREDFV or cerebral redistribution).

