The feeding schedule of each group should be followed regardless of the type of milk available, ventilation status, or presence of an UAC unless specifically requested by the local clinician. The decision to withhold feeds or deviate from the feeding schedule in Tables 2 and 3, because of apparent feed intolerance or clinical deterioration, will also remain at the local clinician's discretion. Gastric residuals are not uncommon in preterm infants [58]. Providing the infant is well and has no abnormal abdominal signs it is usually safe to continue with enteral feeds when gastric aspirate is 2-3 ml or less (2 ml in a baby of less than 750 grams birth weight). If feed volumes are withheld or there is any deviation from the schedule in Tables 2 and 3 then the clinician is free to either start again from day 1, re-start at the volume previously tolerated then increase as scheduled daily, or hold for one or more days at a certain volume and then increase as scheduled.

**Table 2 T2:** Feeding schedule - ml/kg/HOUR

**Day of feeding**	**Volume of milk according to birth weight (ml/kg/HOUR)**				
	
	**< 600 g**	**600-749 g**	**750-999 g**	**1000-1249 g**	**≥ 1250 g**
1	0.5	0.5	0.5	0.5	1.0

2	0.5	0.5	0.5	1.0	1.5

3	0.5	1.0	1.0	1.5	2.0

4	1.0	1.5	1.5	2.0	2.5

5	1.5	2.0	2.0	2.5	3.0

6	2.0	2.5	2.5	3.0	3.5

7	2.5	3.0	3.0	3.5	**4.0 - 4.5**

8	3.0	3.5	3.5	**4.0 - 4.5**	**5.0 - 5.5**

9	3.5	4.0	**4.0 - 4.5**	**5.0 - 5.5**	**6.0 - 6.25**

10	4.0	**4.5 - 5.0**	**5.0 - 5.5**	**6.0 - 6.25**	

11	**4.5 - 5.0**	**5.5 - 6.0**	**6.0 - 6.25**		

12	**5.5 - 6.0**	**6.25**			

13	**6.25**				

14	Increase as required				

(NB feed advancement schedule is *the same *for babies in EARLY or LATE groups: only the timing of initiation of feeds differs)

Where 2 numbers are in a cell separated by a hyphen the first number indicates hourly volume/kg to feed for the first 12 hours of each 24 hour period. The second number in each cell indicates hourly volume/kg to feed for the second 12 hours of each 24 hour period.

Feeds should be given hourly or continuously. However, if there are longer intervals between feeds, e.g. 2 hourly feeds, then the milk volume should be increased accordingly.

Light grey background = feeds increase by 0.5 ml/kg every 12 hours.

Dark grey background = feed volume reached 150 ml/kg/day (6.25 ml/kg/hour).

Feeds can be increased as required.

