### Sample size

Using unpublished data from the Eastern Region Very Low Birthweight database, which suggests a standard deviation of 9 days in the time taken to reach full enteral feeding, about 380 infants will be required to show a difference of 3 days in this outcome with 90% power. The incidence of NEC is about 15% in this population and a sample of 400 would be sufficient to show a reduction to 7.5% with 60% power. NEC is retained as a primary outcome because of its clinical importance for this group of babies. We acknowledge that the power to detect relatively small differences will be limited. The target sample size is 400 babies, to be recruited over 24 months.

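### Allocation is minimised on three factors but no adjustment for them is named in the analysis; followed as written, intervals would be somewhat too wide, and growth is compared as raw change rather than by ANCOVA

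*Protocol article*

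**What the plan says.** In the protocol article, Recruitment and randomisation states: "The program will use minimisation to ensure balance between the groups with respect to hospital of recruitment, gestational age". The sentence goes on to name the gestation cut at 29 completed weeks and the type of Doppler abnormality.

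The Statistical analysis section sets the effect measures. For binary outcomes, which include NEC: "For dichotomous outcomes, relative risks and 95% confidence intervals will be calculated". For continuous outcomes: "For continuous outcomes, differences in means or differences in medians (depending on the distribution of the data) will be calculated", with 95% confidence intervals. Time to full enteral feeding and length of stay go to survival techniques, with no model named. Gestation group and Doppler type appear only as subgroup factors with interaction tests. Hospital does not appear in the analysis at all. The word unadjusted is not used, and adjustment is neither promised nor ruled out.

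Growth, under Secondary outcome measures, is defined as "Change in Z score for weight and head circumference from birth to 36 weeks post"-conceptional age, and also to discharge.

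The Sample size section takes "a standard deviation of 9 days in the time taken to reach full enteral feeding" and concludes that "about 380 infants will be required to show a difference of 3 days in this outcome with 90% power". The target is 400 babies.

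**The concern.** Minimisation forces the arms to be alike on the chosen factors. If those factors predict outcome, the difference between arms varies less from trial to trial than it would under simple randomisation. A standard error that ignores the factors still counts the removed variation, so it is too large: intervals over-cover and tests reject too seldom.

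The article gives reasons to expect some prognostic strength. Its Background calls extreme prematurity the greatest risk factor for NEC and shows feeding practice differing widely between hospitals. Interventions and Other clinical management leave deviations from the schedule, and care in general, to local practice.

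A comparison of raw changes in Z score has a related weakness. In large samples it is never more precise than ANCOVA on the birth value, and it does not properly correct a chance imbalance at birth.

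Precision is what is at stake, along with a clear statement of which analysis is primary before results are seen. Validity is not.

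**Working it through.** **Inputs from the article.** SD 9 days, difference 3 days, 5% two-sided significance, 90% power, target 400; NEC 15% v 7.5%; about 40 hospitals (Feasibility). Equal allocation, 200 per arm, is assumed because the ratio is not stated.

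**Stated figures.**
- Feeding time: n per arm = 2 × (1.960 + 1.282)² × 9² / 3² = 189.1, so 190 per arm and 380 in total, an exact match. At 200 per arm the SE is 9 × √(2/200) = 0.90 days, the 95% half-width is 1.76 days and power is Φ(3/0.90 − 1.96) = 91.5%.
- NEC, 200 per arm: 60.1% with continuity correction, which matches the stated 60% (66.1% without).

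Both are unadjusted two-group calculations, so the stated power does not rely on adjustment.

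**Feeding time treated as a mean.** Let R² be the share of variance explained by the balanced factors; it is not in the documents. After near-perfect balance the true SE is 0.90 × √(1 − R²), while the unadjusted analysis still reports 0.90. Then:
- unadjusted type I error = 2 × [1 − Φ(1.96/√(1 − R²))]
- unadjusted power = Φ((3/0.90 − 1.96)/√(1 − R²))
- adjusted power = Φ(3/(0.90 × √(1 − R²)) − 1.96)

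| Assumed R² | Unadjusted type I error | Half-width, unadjusted v adjusted (days) | Power, unadjusted v adjusted |
|---|---|---|---|
| 0.05 | 4.4% | 1.76 v 1.72 | 92.1% v 92.8% |
| 0.10 | 3.9% | 1.76 v 1.67 | 92.6% v 94.0% |
| 0.20 | 2.8% | 1.76 v 1.58 | 93.8% v 96.1% |
| 0.30 | 1.9% | 1.76 v 1.48 | 95.0% v 97.9% |

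**Simulation of minimised trials.** 400 babies, 40 hospitals and total SD 9, assuming 35% under 29 weeks and 10% with cerebral redistribution. There were 3,000 null trials and 2,000 with a 3-day effect per scenario. The adjusted model held gestation and Doppler type but not hospital.

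| | Weaker factors | Stronger factors |
|---|---|---|
| Assumed gestation effect, Doppler effect, hospital SD (days) | 4, 0, 1.5 | 8, 3, 2 |
| R² of gestation and Doppler type | 0.04 | 0.19 |
| Unadjusted: mean reported SE v actual SD | 0.90 v 0.86 | 0.90 v 0.78 |
| Unadjusted: type I error, coverage | 4.0%, 96.0% | 2.5%, 97.5% |
| Adjusted: mean SE, type I error | 0.88, 4.3% | 0.81, 4.0% |
| Power at 3 days, unadjusted v adjusted | 92.4% v 93.0% | 94.6% v 96.4% |

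The gain is 0.6 and 1.8 points. Adding the hospital share (1.5²/81 = 0.03 and 2²/81 = 0.05) gives total R² of about 0.07 and 0.24. The formula above then predicts unadjusted type I error of 4.2% and 2.5%, in line with the simulation. Omitting hospital explains the conservatism left after adjustment.

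**NEC.** Expected cases at the design rates: 200 × 0.15 + 200 × 0.075 = 45. With an assumed gestation risk ratio of 2, adjusting for gestation (Poisson model, robust errors) moved the SE of the log relative risk from 0.308 to 0.306 and power from 65.3% to 66.7%. With a ratio of 4 the moves were 0.309 to 0.301 and 68.7% to 70.8%.

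**Growth.** Let ρ be the correlation of birth and follow-up Z, and k the birth SD divided by the follow-up SD. ANCOVA variance relative to change-score variance is (1 − ρ²)/(1 + k² − 2ρk). All values of ρ and k are illustrative.
- k = 1: the ratio is (1 + ρ)/2, that is 0.75 at ρ = 0.5 and 0.85 at ρ = 0.7.
- k = 0.7: 0.95 and 1.00.
- k = 0.5: 1.00 and 0.93.

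Eligibility requires birth weight below the 10th centile, which truncates birth-weight Z and makes k below 1 plausible for weight. The gain there is then about 0% to 8% in effective sample size (1/0.927 = 1.08).

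**The case against.** The strongest reply is that the article is silent rather than wrong. A relative risk or a difference in means can be estimated with or without covariates, and the covariate list is commonly left to a full protocol or SAP, neither of which is shown. That stands to this extent: a reader might infer that the trial has committed itself to unadjusted analyses, and the text does not support that. The point is confined to what follows if the section is applied as written. The section does, however, give two of the three factors a role, as subgroup factors only, and it does fix the growth outcome as a change.

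Other limits also stand:
- Feeding time is to be analysed by survival methods. An adjusted hazard ratio is a conditional quantity whose SE need not shrink, so the mean-based figures are only a guide to power.
- A reader might infer that adjustment would repair the admitted 60% power for NEC. A gain of one to two points does not.
- A reader might infer from the equal-SD formula that ANCOVA is worth 18% to 33% more babies (1/0.85 and 1/0.75). That assumes equal spread at birth and follow-up, which the eligibility rule makes doubtful for weight.
- Tables 2 and 3 tie the feeding schedule to birth-weight band, which might suggest adjusting every outcome for band and hospital. Band is not a minimisation factor, and 400 babies over about 40 hospitals is about 10 each, so such models could be unstable with 45 NEC cases or fewer events.

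**Conclusion.** The point holds as a modest loss of precision. Allocation is balanced on three factors, the analysis section names no adjustment for any of them, and applying it literally gives intervals that are somewhat too wide and tests that are conservative. There is no bias, the false-positive rate is not raised, and the stated sample size stands without adjustment.

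In the two simulated scenarios the unadjusted SE was about 5% and 15% larger than the true spread (0.90/0.86 and 0.90/0.78). These sizes rest on assumed prognostic strength, assumed mixes of gestation and Doppler type, equal allocation, and feeding time treated as a mean; with weak factors the loss is negligible. For NEC it is small throughout. For growth, ANCOVA is at least as precise in large samples, but the benefit for weight may be slight.

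**What to change.** In Statistical analysis, state that the primary analyses adjust for gestation group and Doppler type:
- feeding time: a survival model stratified by, or adjusted for, both factors;
- NEC: an adjusted relative risk with robust standard errors;
- hospital: a random effect or cluster term where the model is stable, with a named fallback where it is not;
- unadjusted results shown as supportive.

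Analyse weight and head circumference Z scores by ANCOVA on the birth Z score. The outcome can stay defined as a change, because adjusting change for the birth value gives the same treatment effect as adjusting the follow-up value.

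The cost is wording. The minimisation factors are needed at randomisation, and birth values are already needed to compute the change scores. There are three downsides to acknowledge: hospital terms may be unstable at about 10 babies per site; rare outcomes may need fewer covariates or none; and an adjusted hazard ratio must be reported as a conditional effect.

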### Interim analysis

A Data Monitoring Committee (DMC), independent of the trial investigators, has been established. The DMC terms of reference, including the statistical stopping rules, have been agreed and are documented in the ADEPT DMC Charter. During the period of recruitment to the trial, interim analyses will be supplied in strict confidence to the DMC as frequently as they request. Meetings of the committee will be at least once a year as considered appropriate by the Chair.

In the light of interim data, and other evidence from relevant studies (including updated overviews of the relevant randomised controlled trials), the DMC will inform the Trial Steering Committee, if in their view there is proof beyond reasonable doubt that the data indicate that any part of the protocol under investigation is either clearly indicated or contra-indicated, either for all or for a particular subgroup of trial participants.

Unless modification or cessation of the protocol is recommended by the DMC, the Trial Steering Committee, collaborators and administrative staff (except those who supply the confidential information) will remain ignorant of the results of the interim analysis. Collaborators and all others associated with the study may write through the study co-ordinating centre to the DMC, to draw attention to any concern they may have about the possibility of harm arising from the treatment under study, or about any other matters that may be relevant.

### Establishment of a blinded endpoint committee

As a result of central monitoring the trial data, it has become clear that the primary end point has not been achieved in a small number of cases. There are two main reasons for this:

i) the introduction of breast-feeding

ii) completion of the feeding log has stopped prematurely in the mistaken belief that the primary endpoint has been reached

Where there is uncertainty as to whether the primary endpoint has been reached, a committee has been established to consider each case and recommend an appropriate course of action. The committee will be blind to allocation.

### Sample size

Using unpublished data from the Eastern Region Very Low Birthweight database, which suggests a standard deviation of 9 days in the time taken to reach full enteral feeding, about 380 infants will be required to show a difference of 3 days in this outcome with 90% power. The incidence of NEC is about 15% in this population and a sample of 400 would be sufficient to show a reduction to 7.5% with 60% power. NEC is retained as a primary outcome because of its clinical importance for this group of babies. We acknowledge that the power to detect relatively small differences will be limited. The target sample size is 400 babies, to be recruited over 24 months.

### Feasibility

There is little information on the number of babies that may be eligible for this trial. We estimate that each participating hospital may have around 10-30 eligible babies per year depending on obstetric case mix. If an average hospital has 15 eligible babies per year and a third of these can be recruited (i.e. 5 recruits/hospital/year), around 40 hospitals will need to participate to complete recruitment of 400 babies in 2 years.

### Organisation

The trial will be overseen by a Trial Steering Committee, consisting of the Investigators and the project team at NPEU plus independent members. This group will meet regularly throughout the trial to review progress and resolve problems, receive reports from the Data Monitoring Committee and take decisions about the trial's conduct.

The trial co-ordinating centre will be at the NPEU, where the Trial Co-ordinator will be based. The NPEU will be responsible for day to day co-ordination of the trial, including recruitment of hospitals to the study, programming, data management, and statistical analysis.

### Local co-ordination

Each participating centre will identify a site specific principal investigator to act as local co-ordinator for that centre. Their responsibilities will be to:

i) be familiar with the trial

ii) liaise with the Trial Co-ordinating centre in Oxford

iii) ensure that all staff involved in the care of eligible babies are informed about the trial

iv) ensure that mechanisms for recruitment of eligible babies (including information material) are in place, monitor their effectiveness, and discuss reasons for the non-recruitment with relevant staff

v) ensure that supplies of data collection forms are available, that they are completed and returned to the Trial Co-ordinating centre promptly, and to deal with any queries arising

vi) notify the Trial Co-ordinating centre of any serious adverse events

vii) make all data available for verification, audit and inspection purposes as necessary

viii) ensure that the confidentiality of all information about trial participants is respected by all persons.

## Appendix 1: Modified Bell's criteria from Walsh MC et al 1986

### Stage IA - Suspected NEC

Systemic signs: temperature instability, apnoea, bradycardia, lethargy

Intestinal signs: Elevated pre-gavage residuals, mild abdominal distension, emesis, haem-positive stools

Radiologic signs: Normal or intestinal dilatation, mild ileus

